## Abstract

**Introduction:**

The latest climate reports underscore the importance of climate change mitigation behaviours in reducing greenhouse gas emissions and achieving the climate goals. There is a growing demand among the general population for guidance on sustainable behaviour change. Previous research has indicated that behavioural interventions could play a significant role in facilitating this type of behaviour change. However, the effectiveness of such approaches has yet to be rigorously tested under scientific conditions. This project aims to assess whether a novel, intervention “Sustainable Choices” effectively promotes climate change mitigation behaviours when compared to a control condition.

**Methods:**

Voluntary participants will be recruited from the general population in Sweden and randomized to either “Sustainable Choices”, an online, behavioural intervention targeted at Climate Change Mitigation Behaviours (CCMBs), or a waitlist, both 5 weeks of duration. The target sample size is N = 680. The primary outcome of the study will be pre- to post-intervention difference in climate change mitigation behaviours, measured with the Climate Mitigation Behaviour Scale (CLIMBS). Secondary outcomes will include acceptability measures and effects on psychological well-being. Naturalistic follow-up assessments will be administered at 1-, 3- and 6-months after the post-measurement.

**Discussion:**

The increasing awareness of the link between climate change and individual sustainable lifestyle choices has generated a significant interest in this field. Our aim is to evaluate a scalable intervention targeted at CCMBs, while also promoting psychological well-being associated with sustainable lifestyles.

## Introduction

Scientists agree that human activity is the main cause of ongoing global warming, and that rapid and significant action is needed to reduce emissions and mitigate the changes that are already occurring [1]. Climate change threatens eco-systems as well as human health and welfare, and undermines the achievement of the Sustainable Development Goals [2]. The European Union (EU)’s member states have agreed to target climate change by reducing greenhouse gas (GHG) emissions by 55% by 2030 and reach net-zero emissions by 2050 [3]. On a per-capita perspective, emissions should drop to 1 metric ton dioxide equivalents (CO2e) per-capita between now and 2050 [4], in line with goals defined by the Paris Agreement [5].

### Climate change mitigation behaviours

The Intergovernmental Panel on Climate Change (IPCC) states that systemic changes as well as behavioural changes are needed to meet emission targets and mitigate climate change [1]. It has been shown that accessible, low-cost, climate change mitigation behaviours (CCMBs) could make an immediate and meaningful contribution to this goal and reduce annual per-capita GHG emissions by at least 6–16% [1,6]. CCMBs include, but are not limited to [6]: food choices (e.g., shifting towards plant-based diets), mobility choices (e.g., choosing public transport over car driving or flying), and household energy management (e.g., optimizing residential heating, electricity, and water usage, installation of rooftop solar panels). When taking a broader perspective on individual-level actions and including adoption of new technologies, as well as policy support, the IPCC estimates that CCMBs could reduce GHG emissions globally by 40–70% by 2050 [1].

Large-scale international surveys show that there is a demand in the population for guidance regarding individual CCMBs: Nine out of ten European citizens believe that climate change is a serious problem and agree that GHG emissions should be reduced to a minimum by 2050 [7]. One third of EU citizens feel that they have a responsibility to make sustainable changes in their everyday lives [7]. Two thirds of Americans agree either “strongly” (18%) or “somewhat” (43%) that they feel a personal sense of responsibility to help reduce global warming [8].

### Willingness to act

Repeated international surveys by the Yale Program on Climate Change Communication assess public opinion, knowledge, and behaviours related to climate change. According to their research, the majority of the public in most countries expresses concern about climate change and are willing to take action, but many (46%) feel unsure about what steps to take [9,10]. A representative Swedish survey studied barriers for CCMBs and found that 7 out of 10 respondents believed that their habitual behaviours constituted an obstacle [11]. This indicates that there is a demand for effective actions that individuals can take to contribute to climate change mitigation as well as a need for targeted interventions that facilitate behaviour change.

### Behavioural change interventions

Behavioural change interventions apply a range of well-established techniques, including education, planning, goal setting, reward systems, and problem solving, aimed towards modification of a specific behaviour [12]. There is meta-analytic support that such interventions effectively promote sustainable behaviours with, on average, moderate effect sizes [13,14]. Moreover, recent developments in internet-based interventions for mental health conditions have demonstrated that digital technology has the potential to leverage effective behavioural interventions at scale [15]. However, internet-based methods to deliver interventions that promote climate mitigation behaviours have not yet been tested.

Interestingly, sustainable behaviours have also been found to promote psychological well-being, as suggested by longitudinal observational studies. For example, data from the UK Household Longitudinal Study including 9 000 nationally representative households and over 22 000 individuals during two consecutive years found that household pro-environmental behaviours were predictive of life satisfaction [16]. The link between sustainable behaviours and well-being has also been established cross-culturally in a representative study with data from Brazil, China, Denmark, India, Poland, South Africa, and the United Kingdom (N = 6 969), suggesting that sustainable behaviours and well-being were associated uniformly across all seven countries [17].

### Aims

Considering the available evidence, it seems timely to develop and rigorously test a scalable, internet-delivered intervention targeting individual CCMBs. Our interdisciplinary team has developed an intervention, called ‘Sustainable Choices’, which innovatively combines well-established behavioural change principles and climate science. If ‘Sustainable Choices’ is proven effective at increasing CCMBs, it could be made broadly accessible to the public and thus contribute to meaningful reductions in GHG emissions, facilitate sustainable lifestyles, and improve the overall well-being of individuals on a larger scale. The primary aim of the project is to test whether ‘Sustainable Choices’ is effective in promoting CCMBs, compared to the control group. Secondary aims include exploring whether the intervention is effective in promoting psychological well-being, compared to the control group, whether the intervention acceptable for participants, and whether the effects of the intervention are maintained up to 6 months after the end of the intervention.

## Methods

### Study design

The design of this study is a RCT where participants are allocated (1:1) to an intervention, ‘Sustainable Choices’, or a waitlist control condition for a period of 5 weeks. The primary endpoint for analyses at post-intervention (after 5 weeks). Participants in the control condition are offered to cross-over to the intervention after the primary endpoint. Naturalistic follow-up assessments will be performed 1, 3, and 6 months after the primary endpoint. The trial results will be reported according to CONSORT standards for RCTs [18]. Fig 1 describes the flow of participants with all assessment points.

**Fig 1 pone.0346303.g001:**
[figure not shown]
Study flow chart.

### Participants

Participants are recruited nationally via social media from the general population in Sweden. Interested individuals can register online and answer a series of screening questions. Inclusion criteria are A) 18 years of age or older, B) living in Sweden, C) at least moderate interest in sustainable behaviours (self-rated), and D) able to assign at least one hour per week to the intervention (self-rated). Exclusion criteria are A) lack of ability to read and write in Swedish or B) no regular access to the internet. Eligible participants will then proceed to complete the baseline measures. All participants are required to provide written informed study consent prior to inclusion.

The following variables will be collected to characterize the participant study sample:

The Short-Form Six Audiences of Global Warming is a four-item questionnaire based on research by the Yale Program on Climate Change Communication, categorizing the public into six distinct groups based on their beliefs and concern about climate change [19].

In addition, participants are asked about their age, sex, level of education, geographic region, and residential area (rural area, small urban area, city/larger urban area).

### Interventions

#### Intervention “Sustainable Choices”.

The intervention “Sustainable Choices” has been developed based on knowledge from the climate change mitigation field [1,6,20], behavioural science [12,21], and internet intervention research [21]. The format of the intervention will be similar to a self-paced, online course and consist of texts, pictures and videos, and practical exercises. The content of the intervention is presented online via personal log in, giving access to five modules over five weeks. See Table 1 for a content description of the intervention.

**Table 1 pone.0346303.t001:** Content description of the online course “Sustainable Choices”.

Module	Content	Behavioural change strategies
1) Foundations and core values	This module covers foundational information on climate change and the available mitigation strategies. The participant reflects over individual core values.	Information Reflection
2) Lifestyle	The participant learns more about the GHG emissions connected to the personal lifestyle, high impact choices, and available alternatives.	Information Reflection Goal setting
3) Social networks	This module covers social aspects of climate change mitigation such as talking with others about climate change and reinforcing constructive behaviours.	Information Reflection Goal setting
4) Organizational and democratic processes	The module covers the importance of organizational and democratic processes as pathways for facilitation of sustainable development. It includes workplace-related behaviours as well as strategies for advocacy.	Information Reflection Goal setting
5) Long-term behavioural strategy	In this module, the participant puts together tools from the previous modules and develops an individual long-term strategy.	Goal setting Problem solving Long-term planning Social support

The intervention is hosted by the KI eHealth Core Facility’s technical platform “BASS” (https://ki.se/en/research/ehealth-core-facility).

#### Waitlist control condition.

Participants in the waitlist group will receive a login to the online platform to access a short information page with explanatory information on the timeline of the project and the remaining waiting time for each individual.

### Outcomes

All outcome measures are remotely administered via an online service, which ensures automatic and complete entry of each measure into the trial database. Measurements will be at baseline (week 0), post-intervention (after 5 weeks, primary endpoint), and 1, 3, and 6 months after the intervention (see Fig 1).

#### Primary outcome.

Climate mitigation behaviour will be assessed using the Climate Mitigation Behaviour Scale (CLIMBS), a 23-item instrument developed to capture everyday behaviours directly related to greenhouse gas mitigation [22]. Psychometric evaluation in the baseline sample supported a bifactor structure estimated using a graded response item response theory (IRT) model [22]. The best-fitting solution comprised one general factor reflecting overall mitigation propensity and four orthogonal domain factors: Mobility, Food, Consumption, and Engagement. Model fit indices indicated good fit, and reliability analyses supported a strong general dimension (ω_total ≈ .83; ω_H ≈ .69).

In line with this structure, the primary outcome will be the general CLIMBS latent factor score, estimated using Expected A Posteriori (EAP) scoring from the bifactor graded response model. Domain scores will be computed and analysed as secondary outcomes. The graded response framework accommodates the ordered categorical response formats used across items (frequency, counts, and stage-of-adoption anchors) while allowing estimation of a shared latent structure.

The primary outcome will be the general CLIMBS latent factor (EAP score), reflecting overall climate mitigation behaviour. Domain scores (Mobility, Food, Consumption, Engagement) are treated as secondary/exploratory outcomes, given their coexistence with a strong general factor.

#### Secondary outcomes.

*Psychological well-being* is measured using three measures, capturing general well-being, climate change-related distress, and sense of meaning and purpose.

*General well-being* is measured using the Short Warwick-Edinburgh Mental Wellbeing Scale (SWEMWBS) [23], a 7-item self-report scale that has been widely used within intervention science [24]. Higher scores indicate better subjective wellbeing.

*Climate change-related distress* is measured using two validated, brief measures for low mood (PHQ-2) [25] and worry (GAD-2) [26], adapted following previous research [27]. Both the GAD-2 and PHQ-2 cover the last 2-week period. The adapted GAD-2 includes two questions regarding anxious feelings: “Feeling nervous, anxious, or on the edge because of climate change” and “Not being able to stop or control worrying about climate change”. The PHQ-2 includes two questions regarding “Little interest or pleasure in doing things because of climate change” and “Feeling down, depressed, or hopeless because of climate change”. Higher scores indicate more climate change-related low mood and worry, respectively.

*Meaning and purpose* will be assessed with the NIH-PROMIS Meaning and Purpose—Short Form 6a [28]. This 6-item instrument is part of the Patient-Reported Outcomes Measurement Information System (PROMIS), led by the National Institutes of Health (NIH), and evaluates perceived sense of meaning and purpose in life. Each item is rated on a 5-point Likert scale with responses ranging from “strongly disagree” to “strongly agree” and from “not at all” to “very much.” Higher scores indicate greater levels of meaning and purpose. Raw scores will be converted to standardized T-scores (mean = 50, SD = 10) based on the PROMIS scoring guidelines, enabling comparison to normative reference populations [28].

**Acceptability outcomes** include recruitment rate (number of weekly participant inclusions), participant retention (number of completed intervention modules), and participants’ overall satisfaction with the intervention (using a satisfaction rating for each module). Acceptability outcomes will only be collected once, either during recruitment (recruitment rate, inclusions), during the intervention (retention) or at the post-intervention assessment (satisfaction).

### Sample size

The sample size was determined to detect a between-group difference in the primary outcome (general CLIMBS latent factor score) using a two-sided test of mean differences (α = .05, power = 90%). Assuming a standardized mean difference of g = 0.3 [13], approximately 260 participants per arm are required. Inflating this by 30% to account for expected attrition in behavioural trials resulted in a recruitment target of approximately 680 participants. Sensitivity analyses indicate adequate power for effects in the range g = 0.30–0.40.

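### The stated requirement of about 260 per arm does not follow from g = 0.3 at 90% power (the inputs give 235), and the 1.3 multiplier holds 260 per arm only up to 23.5% loss

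*Protocol article*

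**What the plan says.** The Sample size section of the protocol article bases the calculation on the general CLIMBS factor score, compared between arms with a two-sided test of means at the 5% level and 90% power. It then states: "Assuming a standardized mean difference of g = 0.3 [13], approximately 260 participants per arm are required". The next sentence moves to the recruitment target: "Inflating this by 30% to account for expected attrition in behavioural trials resulted in a recruitment target of approximately 680 participants".

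The Randomization section gives 1:1 allocation. The Study status and timeline section reports that recruitment has closed with 694 participants. The Sample size section names no other input, such as a baseline correlation, a reliability correction, a repeated-measures gain or a second allowance.

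**The concern.** Every input to a standard two-sample calculation is printed, so the result can be checked. The printed result does not match. A gap of about 25 per arm is too large for rounding or for the word approximately to cover.

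The second step raises a separate question. Multiplying a requirement by 1.3 is not the same as protecting it against a 30% loss, which needs division by 0.70. The text speaks of a 30% inflation for expected attrition but does not say what attrition rate is expected.

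What is at stake is how the trial will be read. The article commits to CONSORT reporting, so this justification is likely to be carried into the results paper. If loss exceeds 25% of the 694 recruited, readers would conclude that the trial fell short of its required 260 per arm, although 235 suffices for the power claimed.

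**Working it through.** **Inputs.** Two-sided alpha 0.05, power 0.90, g = 0.3, 260 per arm, 30% inflation and a target of 680 (all from Sample size); 1:1 allocation (Randomization); 694 recruited (Study status and timeline). An equal split and equal loss in the two arms are assumed.

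**The plan's own figures.** The second step reproduces: 260 x 1.30 = 338 per arm, or 520 x 1.30 = 676 in total, which rounds to 680. The inflation was therefore n x 1.3. The first step does not reproduce, as shown next.

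**Requirement for the stated inputs.**
- Normal approximation: n = 2(1.960 + 1.2816)² / 0.3² = 21.016 / 0.09 = 233.5, so 234 per arm.
- Exact noncentral-t calculation: 234.46, so 235 per arm.
- The stated 260 exceeds 235 by 25, about 11%.

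**Search for a variant that gives 260.**

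| Power | Two-sided, per arm | One-sided, per arm |
|---|---|---|
| 80% | 176 | 139 |
| 85% | 201 | 161 |
| 90% | 235 | 191 |
| 95% | 290 | 242 |

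The small-sample (Hedges) correction moves the normal-approximation figure only to 233 or 235. An unstated 10% allowance would fit (234 / 0.9 = 260), but the article mentions none, and attrition is added only afterwards.

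**What 260 per arm delivers.** Power at g = 0.3 is 92.7%. The effect detectable with 90% power is g = 0.285.

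**The inflation step.**
- If 30% attrition is meant: 340 x 0.70 = 238 per arm remain from 680. Keeping 260 would need 520 / 0.70 = 743 in total (372 per arm, 744, when rounded up by arm).
- Loss at which 260 per arm is still kept: 1 - 260/340 = 23.5% from 680, and 1 - 260/347 = 25% from 694.
- Inflating the correct requirement by division: 235 / 0.70 = 335.7, so 336 per arm, 672 in total.

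**Power at g = 0.3 after 30% loss.**

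| Randomized | Left per arm | Power |
|---|---|---|
| 680 | 238 | 90.4% |
| 694 | 347 x 0.70 = 242.9, about 243 | 91.0% |

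**The case against.** The best defence is that nothing depends on the discrepancy. The figure of 260 is too high, so the error is conservative. The properly derived total of 672 is about 1% below the target of 680, and recruitment closed above both. That stands, and it sets the severity.

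The second defence concerns attrition. The article states an inflation factor ("Inflating this by 30% to account for expected attrition in behavioural trials") and no attrition rate. Taken literally, 260 x 1.3 is correct arithmetic, and it protects 260 per arm against any loss up to 23.5%. This also stands. Reading the 30% as the expected loss is natural but remains an assumption, so this part of the point is conditional.

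Three stronger readings are tempting, and the document supports none of them.
- A reader might infer that the trial is underpowered. It is not at g = 0.3, even after 30% loss.
- A reader might infer that the section contradicts itself, or that the planned number cannot be identified. The chain from 260 per arm through 1.3 to about 680 is consistent, and the target also appears in the Abstract. Only the link from g = 0.3 to 260 fails.
- A reader might fault the power statement, "Sensitivity analyses indicate adequate power for effects in the range g = 0.30–0.40", for starting at the planning value. The statement is true: at 238 per arm, power is 90.4% at 0.30 and 99.2% at 0.40. The article claims nothing about smaller effects, and asking for them would be a preference.

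**Conclusion.** The point holds as a minor reporting error. The printed inputs give 235 per arm, not about 260. This part rests only on the stated test, alpha, power and effect size, with equal arms.

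The attrition part is conditional. If 30% loss is expected, the 1.3 multiplier leaves 238 per arm from 680, short of the 260 called for. If the expected loss is 23.5% or less, 680 does keep 260. The document does not settle which is meant, and it does not settle whether 260 reflects an unreported allowance or a slip.

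Under the 30% reading the two steps roughly offset each other: too large a requirement is followed by too small an inflation. The target therefore still gives about 90% power at g = 0.3. The design, the analysis and the adequacy of the recruited number are unaffected.

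**What to change.** Revise the Sample size section as follows:

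1. Give the requirement as 235 evaluable participants per arm, or keep 260 and state the additional assumption that produces it.
2. State the expected attrition rate and inflate by 1/(1 - rate). At 30% this gives 336 per arm, 672 in total, which is consistent with the target of 680.
3. Report that the 694 recruited, with 30% loss, leave about 243 per arm and 91% power at g = 0.3.

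The statement on power for g = 0.30 to 0.40 can stay. The cost is a few sentences of text. No participants need to be added, and the design and analysis do not change.

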### Randomization

Participants are randomly assigned on a 1:1 ratio to either arm (intervention or control). The randomization sequence is created through a digital randomization algorithm (random.org) and handled by an external administrator outside of the research team to ensure integrity of the randomization procedure.

### Blinding

All outcome measures in this trial will be based on self-reported questionnaires completed directly by participants. As no external assessors will be involved in the data collection, blinding of outcome assessors is not applicable.

### Statistical methods

The principal analyses will follow an intent-to-treat statistical analysis plan.

Patterns and extent of missing data will be examined descriptively, including proportions of missingness per variable and associations with observed participant characteristics. CLIMBS item-level missingness will be handled directly within the graded response IRT framework using marginal maximum likelihood estimation, which accommodates incomplete response patterns under the assumption of missing at random (MAR). No imputation of item responses is planned. If missingness in covariates or outcome data exceeds trivial levels, appropriate model-based methods consistent with the assumed missingness mechanism will be applied.

CLIMBS will be analysed using a bifactor graded response IRT model to obtain a general mitigation behaviour score on a common metric across trial arms and assessment waves. Item parameters will be estimated jointly (not separately by arm). Intervention effects will be tested using mixed-effects models with participant-level random intercepts (or equivalent marginal approaches) to account for within-person correlation over repeated assessments. The primary analyses will use the general factor CLIMBS score as the dependent variable. Sensitivity analyses using the unit-weighted total score will be conducted to assess robustness of findings. All randomized participants will be included in regression analyses, with separate analyses for all continuous primary and secondary outcomes and time and group as predictor variables. Between-group effect sizes at the primary endpoint will be estimated using Cohen’s *d*. In addition, a Complier Average Causal Effect (CACE) analysis will be conducted to estimate the causal effect of the intervention among participants who complied with their assignment (“compliers”). The original randomization will be used as an instrumental variable to account for potential bias due to selective participation. The CACE will be estimated using two-stage least squares (2SLS) regression with the CLIMBS general factor as the outcome. This analysis will be reported as a secondary, complementary analysis. The naturalistic follow-up (1, 3 and 6 months) will be analysed as within-group regression analyses in the intervention group, to test for maintenance of intervention effects on all outcome measures.

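### The primary model is described by time and group, without naming the group-by-time term, the use of baseline, or the coefficient that tests the week-5 effect

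*Protocol article*

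**What the plan says.** All of this is in the Protocol article.

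- **Model** (Statistical methods): "Intervention effects will be tested using mixed-effects models with participant-level random intercepts (or equivalent marginal approaches"), with within-person correlation over the repeated assessments as the reason.
- **Predictors** (same section): all randomised participants enter the regressions, "with separate analyses for all continuous primary and secondary outcomes and time and group as predictor variables". No interaction, baseline covariate, baseline constraint or primary contrast is named.
- **Waves**: the 1-, 3- and 6-month assessments are analysed separately, within the intervention group. The between-group model therefore has two waves, baseline and week 5.
- **Target**: the Abstract (Methods) states, "The primary outcome of the study will be pre- to post-intervention difference in climate change mitigation behaviours". The Outcomes section places the primary endpoint at "post-intervention (after 5 weeks, primary endpoint").
- **Effect size** (Statistical methods): "Between-group effect sizes at the primary endpoint will be estimated using Cohen’s" *d*. The article does not say how *d* relates to the model.
- **Sample size**: about 260 per arm, "using a two-sided test of mean differences (α = .05, power = 90"%). The effect is stated as "Assuming a standardized mean difference of g = 0.3". Inflation for 30% attrition leads to about 680 in total.

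**The concern.** When baseline is one of the repeated responses, a model with time and group alone forces the arms to differ by the same amount at both waves. Its group coefficient is then a weighted average of the baseline difference, which is zero in expectation under randomisation, and the week-5 difference. That is not the quantity the trial was sized for. If a group-by-time term is fitted as well, the group coefficient becomes the baseline difference and the interaction carries the effect. The two readings test the primary hypothesis with different coefficients, and the article does not say which applies. Under the second reading, leaving the baseline means free ignores that randomisation makes them equal, which costs some precision.

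**Working it through.** **1. The plan's own figure.** With effect 0.3, SD 1, two-sided alpha 0.05 and 90% power, n per arm = 2(1.960 + 1.282)²/0.3² = 234. The stated 260 is not reproduced; 260 would give 92.8% power. The total is close to 260 × 1.3 × 2 = 676. With 340 per arm and 30% lost, 0.7 × 340 = 238 per arm remain, and a plain week-5 comparison has 90.5% power. The size is therefore adequate for that comparison, and the question here is which coefficient is tested.

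**2. Inputs.** From the article: N = 340 per arm (680/2), fraction observed at week 5 q = 0.7, true difference 0 at baseline and 0.30 at week 5. Assumed: SD 1 at both waves and pre-post correlation ρ from 0.5 to 0.8, which the article does not give. Power is Φ(coefficient/SE − 1.96).

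**3. Formulas (generalised least squares, two waves).**

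- Time + group: expected group coefficient = 0.30q / [(1+ρ) + q(1−ρ)]; variance = 2(1+ρ) / {N[(1+ρ) + q(1−ρ)]}.
- Time + group + group-by-time, baseline free: expected interaction = 0.30; variance = 2(1−ρ²)/(qN) + 2(1−ρ)²/N.
- Time + group-by-time, common baseline mean: expected effect = 0.30; variance = 2(1−ρ²)/(qN).

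**4. Complete data (q = 1), literal reading.** 0.30/[(1+ρ) + (1−ρ)] = 0.30/2 = 0.15, whatever ρ is. The halving needs no assumed correlation.

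**5. With 30% missing at week 5.** Example at ρ = 0.5:

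- Literal: coefficient 0.21/(1.5 + 0.35) = 0.114; SE = √[3/(340 × 1.85)] = 0.0691.
- Baseline free: SE = √(1.5/238 + 0.5/340) = 0.0882.
- Common baseline: SE = √(1.5/238) = 0.0794.

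| ρ | Literal: coefficient | Literal: power | Interaction, baseline free: SE | Power | Common baseline: SE | Excess variance, free vs common |
|---|---|---|---|---|---|---|
| 0.5 | 0.114 | 38% | 0.0882 | 92.5% | 0.0794 | 23% |
| 0.6 | 0.112 | 35% | 0.0795 | 96.5% | 0.0733 | 17.5% |
| 0.7 | 0.110 | 33% | 0.0694 | 99% | 0.0655 | 12% |
| 0.8 | 0.108 | 31% | 0.0571 | >99% | 0.0550 | 8% |

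The last column is q(1−ρ)/(1+ρ), for example 0.7 × 0.5/1.5 = 0.23.

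**6. Sensitivity below that range.** At ρ = 0.3 the literal reading gives 0.117 and 43% power. The interaction with a free baseline gives 83%, and the common-baseline model 93%.

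**The case against.** The strongest reply is that the article lists predictor variables, not model terms. It does not exclude an interaction and does not say that the group main effect is the test. It also mentions missing covariate data, so the two predictors may not be the whole model. The pre-to-post outcome, the week-5 endpoint, the powered between-group difference and the effect size at the endpoint all fit a model with group-by-time and fit main effects alone badly. The article condenses a fuller plan, and a statistical analysis plan that is not shown may write the model out.

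Most of this stands. A reader might infer that the trial is committed to a main-effects model and has about a third of the power it claims. The article does not support that: the dilution arises only if no interaction is fitted and the group coefficient is taken as the test. Nor does the dilution add to the variance penalty, since one needs a model without the interaction and the other a model with it. A free-baseline interaction model is standard and valid; the objection to it concerns precision, not bias. A reader might also infer that Cohen's *d* will come from raw means of completers. The article does not say so.

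What the reply does not remove is that the section states the predictors, and goes as far as naming two-stage least squares for a secondary analysis, yet leaves the primary coefficient unidentified. The words it does use describe, on their face, a model that misses the endpoint.

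**Conclusion.** The point holds as a defect in how the primary test is stated. Read literally, the group coefficient would be 0.15 instead of 0.30 with complete data. It would be about 0.11, with 31-38% power, given 340 per arm, 30% loss at week 5 and an assumed correlation of 0.5 to 0.8. Those power figures describe the literal reading only. On the more likely reading, with group-by-time, the estimate is unbiased and power is about 92% or more at the same correlations. What remains is an avoidable 8-23% excess in variance from leaving the baseline means free. The power and variance figures depend on the assumed correlation and on equal SDs at the two waves; the halving with complete data does not depend on the correlation.

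**What to change.** State the primary between-group model as a random-intercept (or equivalent marginal) model on baseline and week 5 with fixed effects for time and group-by-time and a common baseline mean, so that no group term applies at baseline. An equivalent adjustment for baseline CLIMBS would also serve; the constrained form has the advantage of keeping randomised participants who lack a week-5 score, in line with the article's aim of including everyone randomised. Name the group difference at week 5 as the single primary test. Derive Cohen's *d* from that contrast, divided by a stated SD such as the pooled baseline SD. Use the same form for the continuous secondary outcomes measured at both waves.

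The cost is one paragraph in the protocol or analysis plan. Baseline is already collected, so no new data are needed. Recruitment is complete, so the wording should be settled before the between-group analysis is run.
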